### 8.1 SAMPLE SIZE CALCULATIONS

We hypothesize that there will be a minimum 20% difference in the proportion of subjects who pass OSCE A and OSCE B, via a one-sided test at the 6-month evaluation. The desired power is 80% taking into account that two comparisons (VR vs. Controls and Video vs. Controls) will be carried out with the hypothesis that the proportions of subjects in the VR group will demonstrate performance metrics that are higher (by at least 20%) than the control group.

The alpha level has been halved so as not to inflate the type-1 error rate (of 5% overall) so 83 participants per group or a total of 249 participants will be sufficient to detect this difference under all the scenarios considered here. However, to account for study dropout, we will recruit up to 280 participants across the two country sites. We expect that the power generated by the ANCOVA procedure will be even higher as well as the power generated by the longitudinal (secondary) change-point analyses will be much more sensitive (powerful) to detect differences in each pairwise comparison. Thus the proposed sample size will likely be able to detect difference in skill retention with very high power.

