## 8. DATA ANALYSIS

Demographic data will be compared between VR, NR video, and control groups and assessed for group to group differences. Pass/Fail rates on the study evaluations: Knowledge test, bag-and-mask ventilation skills assessment (BMV), and standardized simulations of routine care and initial resuscitation (OSCE A) and prolonged resuscitation (OSCE B) done at the following time periods: Baseline, Pre-course, Immediate post-course, and at 1 month, 3 months, and 6 months in the follow up period will be calculated and compared between groups. The primary endpoint is the 6-month post-baseline evaluation. We will perform an analysis of covariance with each six-month score regressed on the baseline score of each subject and compared among the three groups.

Two post-hoc statistical tests will be performed to ascertain possible statistically significant differences between VR and Video groups with the Control group at each time point. A secondary analysis will take full advantage of the longitudinal nature of the data (see Figure 9). Here, we posit a structural response model where skills will be initially acquired uniformly by all subjects (at the immediate post-course assessment after face-to-face training) but retention of these skills will dissipate rapidly over time in the Control group, but less precipitously in the other two groups, with the least deterioration of knowledge and skills in the VR group. The statistical modeling approach in this case will be through a change-point model with random intercept and slope. The main statistical test will be the assessment of the statistical significance of the interaction between group and time, during the second period (i.e., after the change or inflection point in the curve).

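### The 5% overall error claimed in Section 8.1 covers two comparisons on one outcome, but Section 8 makes all four 6-month evaluations primary without naming one

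*Protocol*

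**What the plan says.** Protocol Section 8.1 sizes the trial on a "minimum 20% difference in the proportion of subjects who pass OSCE A and OSCE B, via a one-sided test at the 6-month evaluation". It states that "two comparisons (VR vs. Controls and Video vs. Controls) will be carried out" and deals with that multiplicity as follows: "The alpha level has been halved so as not to inflate the type-1 error rate (of 5% overall"). The group size rests on this: "83 participants per group or a total of 249 participants will be sufficient to detect this difference under all the scenarios considered here".

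Protocol Section 8 lists four evaluations to be compared between groups: the knowledge test, BMV, OSCE A and OSCE B. It fixes 6 months as the primary time but does not say which of the four is the primary outcome. The primary method is "an analysis of covariance with each six-month score regressed on the baseline score of each subject", with the three groups compared. Two tests, described as post-hoc, then look for "differences between VR and Video groups with the Control group at each time point". The longitudinal change-point model is labelled secondary. Neither section gives an order of testing, a both-must-succeed rule or an adjustment across the four evaluations.

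**The concern.** Halving alpha is the right correction for two arm comparisons on one outcome at one time. Section 8 describes something wider: four 6-month outcomes of equal standing, each with the same two comparisons against Control, or eight tests. The correction does not count that factor of four. As written, success of VR or video could be claimed on whichever of the four instruments reached significance, while the report cited a 5% overall error that the plan does not deliver. The sizing is exposed as well, because 83 per group is built on the 0.025 level.

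**Working it through.** **Inputs from the protocol.** Overall error 5%, halved to 0.025 per comparison; one-sided test; two comparisons with Control; four instruments; primary time 6 months; 83 per group; 80% power; 20-point difference (read as absolute).

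**Inputs assumed.** The correlation between instruments is not given, so 0 to 0.9 is shown. The control pass rate is not given, so 20% and 40% are used where a sample size is needed. All error rates are under no effect of either intervention on any instrument.

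**Step 1: reproduce the plan's figures.**
- Error: 2 × 0.025 = 0.05, the stated 5%.
- Size: n = [z(0.975)·√(2p̄q̄) + z(0.80)·√(p₁q₁ + p₂q₂)]² / 0.20². For 20% vs 40%: [1.960·√0.42 + 0.842·√0.40]² / 0.04 = 81.2, so 82 per group. With a continuity correction, 15% vs 35% gives exactly 83. The stated 83 is consistent with one-sided 0.025 per comparison.

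**Step 2: one outcome, two comparisons.** The two contrasts share the control arm, so with equal groups they correlate at 0.5. The error is 1 − Φ₂(1.96, 1.96; 0.5) = 4.5% (4.9% if they were independent: 1 − 0.975²). The halving works here.

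**Step 3: more than one outcome at 6 months.** The upper bound for eight tests is 8 × 0.025 = 20%. With uncorrelated instruments and a shared control:
- two outcomes: 1 − (1 − 0.0454)² = 8.9%
- four outcomes: 1 − (1 − 0.0454)⁴ = 17.0%

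For correlated instruments, normal test statistics were simulated for three equal arms. The gated columns count a pairwise rejection only if that instrument's three-group test is significant at 5%. Simulation error is about 0.1 point.

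| Correlation between instruments | OSCE A and B separately | Four instruments | OSCE A and B, gated | Four instruments, gated |
|---|---|---|---|---|
| 0 | 8.9% | 17.0% | 4.1% | 8.0% |
| 0.3 | 8.6% | 15.3% | 4.0% | 7.5% |
| 0.5 | 8.1% | 13.7% | 3.9% | 6.8% |
| 0.7 | 7.4% | 11.3% | 3.6% | 5.8% |
| 0.9 | 6.3% | 8.2% | 3.0% | 4.1% |

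Without a gate, four instruments exceed 5% at every correlation shown. With a gate, they exceed 5% up to correlation 0.7.

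**Step 4: what a wider split of alpha would cost.** Bonferroni over eight tests gives 0.05/8 = 0.00625 one-sided. The Step 1 formula then needs 116 per group at 20% vs 40% and 138 at 40% vs 60%. At that level, 83 per group has 63% and 53% power.

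**The case against.** **The sizing phrase may mean one outcome.** Section 8.1 speaks of a single proportion of subjects who pass OSCE A and OSCE B. If that means passing both, there is one binary outcome with two tests, the error is 4.5%, and the halving is correct for the endpoint it sizes. This reading is natural and it stands. It follows that the two OSCEs in Section 8.1 cannot simply be charged as two separate outcomes. It does not rescue Section 8, which lists the OSCEs as separate evaluations, analyses each score and defines no combined outcome.

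**The three-group ANCOVA may act as a gate.** Calling the pairwise tests post-hoc, after a three-group comparison, suggests they follow only a significant overall result. This would cut the inflation substantially and bring the two OSCEs alone inside 5%. The protocol does not state the condition, however, and a gate applied to each instrument separately does not reliably hold 5% across four.

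**The time points.** Because the pairwise tests are repeated at each visit, a reader might infer that every visit multiplies the error behind the 5% claim. The documents do not support that. Section 8 fixes 6 months as primary, and Section 8.1 ties its test to the 6-month evaluation. The other visits can be read as secondary and need only be labelled so.

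**A statistical analysis plan may settle it.** It may, and missing detail is not the complaint. The protocol itself states the 5% and the multi-instrument primary evaluation, and the two do not agree.

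**Conclusion.** The point holds for the four instruments at 6 months. The 5% overall statement is true if a single outcome carries the claim (4.5%). Taken with Section 8 as written, it is not: the family-wise error is about 8% to 17% for assumed correlations of 0.9 to 0, or about 4% to 8% under an unstated 5% gate. The range reflects both the unknown correlation and the unsettled reading of Section 8. These figures assume one-sided 0.025 per test, equal groups, a shared control and no true effect on any instrument.

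Two further inferences would go too far. The halving is not wrong for the endpoint that Section 8.1 sizes if passing both OSCEs is meant. Nor does this point show that more participants are needed, since with one named outcome the multiplicity calls for none.

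**What to change.** In Section 8, name one primary outcome consistent with the sizing in Section 8.1: the proportion of participants passing both OSCE A and OSCE B at the 6-month assessment. Test VR against Control and Video against Control on it, each at one-sided 0.025, and call these planned contrasts rather than post-hoc tests. State that the separate OSCE scores, BMV, knowledge and all other time points are secondary and outside the 5% claim. Use the same definition of the outcome in Section 8.1.

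Because the named outcome is a proportion, the ANCOVA of the individual scores would become a secondary analysis under this wording.

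The cost is protocol text, and the group size does not change on account of multiplicity. The real loss is that a positive result on BMV or knowledge alone is no longer a primary success. Keeping all four instruments primary and splitting alpha across eight tests would instead require the larger groups in Step 4, or accept the lower power shown there.

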### 3. STUDY OBJECTIVE

The primary objective is to assess the impact of mobile VR simulation used before and after initial NR training on neonatal resuscitation educational indicators and performance outcomes in healthcare providers, in comparison to traditional HBB training.

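### Section 8.1 halves alpha between the two arm contrasts with no step-down; Holm's procedure keeps the same 5% error and never rejects less

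*Protocol*

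**What the plan says.** Section 3 (Study Objective) concerns VR alone: "The primary objective is to assess the impact of mobile VR simulation used before and after initial NR training", with outcomes judged "in comparison to traditional HBB training". Video is not mentioned there.

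Section 8.1 (Sample size calculations) plans two contrasts against Control: "two comparisons (VR vs. Controls and Video vs. Controls) will be carried out". The 20-point hypothesis in the same sentence is worded for VR only: "with the hypothesis that the proportions of subjects in the VR group will demonstrate performance metrics that are higher (by at least 20" percent than control. Testing is "via a one-sided test at the 6-month evaluation". The adjustment is the halving: "The alpha level has been halved so as not to inflate the type-1 error rate (of 5% overall". That makes 0.025 one-sided per contrast, and the section arrives at 83 per group, 249 in all, for 80% power.

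Section 8 (Data analysis) compares the three groups by analysis of covariance at 6 months and then puts the pairwise tests on an equal footing: "Two post-hoc statistical tests will be performed to ascertain possible statistically significant differences between VR and Video groups with the Control group". It expects VR to retain skills best, Video next and Control least. Neither section gives a testing order or says that unused alpha passes from one contrast to the other.

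**The concern.** When two hypotheses share 5% by a fixed split, each stays at 0.025 even after the other has been rejected. At that point only one null hypothesis can still be true, and 0.05 is available for it. Leaving the level at 0.025 gives up power without buying any protection against false positives.

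What is at stake is efficiency. The validity of the trial is not in question. The loss falls mainly on the second claim once the first is won, and is largest when both interventions work. A smaller matter goes with it: the objective and the sample-size hypothesis concern VR, but no sentence says that VR vs Control is the contrast that answers the objective.

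**Working it through.** **Inputs.** From Section 8.1: 83 per group, a 20-point difference in pass proportion, one-sided testing, 5% overall, two contrasts, 80% power. The control pass rate is not given, so a range of 20-60% is assumed. The Video effect is not given either, so 0, +10 and +20 points are tried.

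**The plan's own figure.** With pooled variance,

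n = [z(1−α)·√(2·p̄·(1−p̄)) + z(0.80)·√(p1(1−p1) + p2(1−p2))]² / (p2−p1)².

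For 60% vs 80% at α = 0.025: [1.960·√0.42 + 0.842·√0.40]² / 0.04 = (1.270 + 0.532)² / 0.04 = 81.2, so 82 per group. That is within one of the stated 83. The mirror case, 20% vs 40%, gives the same. Power at 83 is then 80.9%. The figure therefore fits the halved alpha, under an assumed control rate.

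**Why Holm keeps the error.** If both nulls are true, a false rejection needs the smaller p-value to be at or below 0.025, which has probability at most 0.025 + 0.025 = 0.05. If only one null is true, it is never tested above 0.05. No assumption about the correlation from the shared control is needed.

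**Why Holm never rejects less.** Holm rejects VR if z(VR) > 1.960, as the split does, and also if z(VR) > 1.645 while z(Video) > 1.960. The same holds with the arms exchanged.

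**Size.** 400,000 simulated three-arm trials per scenario, 83 per arm, shared control, pooled z tests. Entries are percentages, split / Holm.

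| Control pass rate | Both +20: VR | Both +20: both significant | VR +20, Video +10: VR | VR +20, Video +10: Video | VR +20, Video 0: VR |
|---|---|---|---|---|---|
| 20% | 81.4 / 86.4 | 70.5 / 80.6 | 81.5 / 82.4 | 32.0 / 43.0 | 81.4 / 81.4 |
| 30% | 75.1 / 80.6 | 62.0 / 73.1 | 75.0 / 76.0 | 27.0 / 36.3 | 75.1 / 75.1 |
| 40% | 74.2 / 79.7 | 61.1 / 72.1 | 74.4 / 75.4 | 25.5 / 34.9 | 74.3 / 74.3 |
| 50% | 75.3 / 80.7 | 62.6 / 73.5 | 75.1 / 76.0 | 25.5 / 35.0 | 75.1 / 75.2 |
| 60% | 81.4 / 86.2 | 70.8 / 80.6 | 81.5 / 82.2 | 26.9 / 36.9 | 81.4 / 81.4 |

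When both arms are +20, Video's power matches VR's by symmetry. A check at 40%: the chance of at least one rejection is 87.4% under either rule, so power for both is 74.2 + 74.2 − 87.4 = 61.0% for the split and 79.7 + 79.7 − 87.4 = 72.0% for Holm, which agrees with the table to rounding.

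With no effect in either arm, the chance of any rejection is 4.4-4.8% and is the same for both rules.

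**VR tested first at 0.05, then Video at 0.05.** VR power is 83-89%. If only Video works, Video power falls from 74-81% under the split to about 5%.

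**The case against.** Five objections deserve an answer.

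- **The halving is valid.** This stands. It is a correct Bonferroni split, and a reader who infers an error in type I control would be mistaken.
- **The sentence sits in the sample-size section and does not say alpha is halved permanently.** This stands in part. Sizing at 0.025 is also what a Holm plan would do, because Holm's first step is at 0.025, and an analysis plan not shown could add the second step. A reader might infer that step-down testing is ruled out; the text does not say so. But the halving is the only rule stated, and replacing it is an improvement that does not depend on missing detail.
- **The gain for VR is small where it matters.** This stands. Section 8 expects Video to fall between VR and Control. At Video +10, VR gains about 1 point under Holm; with no Video effect it gains nothing. The 5-point gain needs Video at +20, which the protocol does not posit. Nor is winning both contrasts a stated power target.
- **Video ahead with VR not ahead has a reading.** This stands. A reader might infer that such a result is undefined. Each null is tested separately, so it would mean that Video is superior and the VR objective is not met. Section 3 already implies which contrast matters, and naming it is mostly labelling.
- **The figures use pass rates, while Section 8 plans analysis of covariance on scores.** The sizes carry over only approximately. The ordering of the two procedures holds for any pair of valid p-values.

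A VR-first sequence may also look like the natural remedy. It is a trade-off: its gain for VR is paid for by losing the Video claim whenever VR fails, and Section 8.1 plans both contrasts.

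**Conclusion.** The point holds as a matter of efficiency. The stated split is valid, and Holm dominates it at the same overall 5%. If both arms are +20 points, the gain is about 5 points of power per contrast and about 10-11 points for winning both. If Video is +10, it is about 9-11 points for Video and about 1 for VR. If Video has no effect, VR power is unchanged.

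These sizes rest on 83 analysed per arm, pooled z tests, and assumed control rates of 20-60%. That Holm rejects at least as often rests on none of them. At control rates of 30-50% the split gives VR 74-75% power, which a reader might take as proof that the halving makes the trial underpowered. The protocol does not support that: its control rate is unstated, and at 20% or 60% the split meets 80%.

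The point covers only the two arm contrasts at 6 months. It does not address multiplicity across OSCE A and OSCE B or across time points.

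**What to change.** In Sections 8 and 8.1:

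- Keep the sample size computed at one-sided 0.025.
- State that the two 6-month contrasts against Control are tested by Holm: the smaller one-sided p-value at 0.025 and, only if it is significant, the other at 0.05.
- State that VR vs Control is the contrast that answers the objective in Section 3.

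This takes a few sentences and no added participants or data. The only downside is that simultaneous confidence limits matching Holm are less simple than those matching a fixed split.

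A fixed sequence with VR first remains open to the sponsor as a preference, given its price for the Video claim. It is not part of this recommendation.

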## 9. QUALITATIVE STUDIES

This will consist of focus groups and key informant interviews led by an experienced facilitator utilizing semi-structured questionnaires. We will conduct 4-6 focus groups each consisting of 6-8 study participants and up to 15-20 key informant interviews among NR trained HCPs enrolled in the study and a convenience sample of key stakeholders within Nigeria such as health facility administrators and community-based stakeholders.

Domains addressed will include: what exposure to VR do healthcare providers have currently and what are their thoughts about learning from VR? How and when do healthcare providers use VR and what are their perspectives on it? What are the barriers and facilitators to using VR for initial and refresher training?

Sessions will be digitally recorded and transcribed. The data will be organized using qualitative analysis software. Qualitative data will be analyzed by two study investigators experienced in thematic analysis. Investigators will independently review all FGD transcripts to identify initial themes then work together to build consensus on all major themes. They will then independently code all transcripts through an iterative process using thematic content analysis. As new codes are identified, the coding scheme will be refined using the grounded theory constant comparative method.

Investigators will meet regularly to compare and discuss codes, resolve disagreements, and come to consensus on discordantly coded data. Saturation will be achieved after no new themes emerge from the data. Codes within and across transcripts will be compared and synthesized into overarching themes that reflect the perspectives of healthcare providers on the use of technology and VR for training. A random sample of transcripts will be double coded to ensure agreement between coders. The data will be used to prepare a report on the facilitators and barriers to VR training for NR initial and refresher training in LMICs from the perspective of participants and stakeholders. The results will be shared with a subset of the participants for verification.

## APPENDICES

### APPENDIX 1. ABBREVIATIONS/DEFINITION OF TERMS

AAP = American Academy of Pediatrics  
BMGF = Bill and Melinda Gates Foundation  
BMV = bag-and-mask ventilation  
DHIS2 = District Health Information Software  
eHBB = mobile/virtual reality Helping Babies Breathe  
ECEB = Essential Care for Every Baby  
ECSB = Essential Care for Small Babies  
ENAP = Essential newborn action plan  
ETAT+ = Emergency triage, assessment, and Treatment plus admission  
HBB = Helping Babies Breathe  
HBS = Helping Babies Survive  
HCPs = Health care providers  
LDHF = Low dose, high-frequency  
LIFE = Life-saving Instruction for Emergencies  
LMICs = Low/Middle income countries  
mHBS = mobile Helping Babies Survive  
MOH = Ministry of Health  
MNCH = maternal newborn child health  
NMR = neonatal mortality rate  
NR = neonatal resuscitation  
NRP = Neonatal Resuscitation Program  
OSCE = Objective Structured Clinical Examination  
PPV = positive-pressure ventilation  
TOTs = Training of Trainers  
VR = virtual reality  
WHO = World Health Organization

#### Definition of Terms

**3D simulation:** These screen-based training scenarios are similar to the NRP eSIM® scenarios or the LIFE mobile game that enables learners practice the algorithm (e.g., “The Action Plan”) and reinforces knowledge of NR pathways but do not require a VR headset.

**VR simulation:** These training scenarios enable learners to practice both the NR algorithm and skills required for NR such as with the LIFE immersive VR NR game using a VR headset with or without hand controllers, e.g. Google cardboard, Google Daydream, Oculus Rift or HTC Vive.

**Educational video:** This is a video showing recommended NR algorithms, skills, and/or performance competencies related to preparation for delivery, immediate care at birth and/or successful newborn resuscitation using recommended HBB practices, such as videos offered by Global Health Media.

APPENDIX 2. STUDY DIAGRAM

[figure not shown]

eHBB+mHBS/DHIS2 v.1

**APPENDIX 5. PARTICIPANT SURVEYS**

Confidential

eHBB Project  
Page 1 of 4

# Demographic Survey

Study ID

**Please complete the following survey**

1. Age range

☐ less than 21 years   ☐ 21 - 30 years   ☐ 31 - 40 years   ☐ 41 - 50 years   ☐ More than 50 years

2. Sex

☐ Male   ☐ Female

3. Profession

☐ Consultant physician  
☐ Senior registrar  
☐ Registrar  
☐ Nurse  
☐ Midwife  
☐ Clinical Officer  
☐ Other

profession\_other

Please list your Degree/Certification in your area of practice

4. Years of practice since completion of training

☐ Less than 5 years   ☐ 5 - 10 years   ☐ 11 - 15 years   ☐ 16 - 20 years   ☐ More than 20 years

5. Current location of practice

☐ Nigeria   ☐ Kenya   ☐ Other

Other (please specify)

6. Health care level of practice

☐ Government (Tertiary care)  
☐ Government (Secondary care)  
☐ Government (Primary care)  
☐ Private  
☐ Faith-based facility

Healthcare Facility

Confidential

Page 2 of 4

7. Specialty (if applicable)

- ☐ General Paediatrics  
☐ Subspecialty Paediatrics  
☐ Obstetrics & Gynaecology  
☐ Subspecialty O & G  
☐ Other specialty

Other Specialty (please specify)

8. Does your institution/health facility have facilities for simulation based training?

- ☐ Yes ☐ No

9. In what capacity does your institution use simulation-based training?

- ☐ Teaching ☐ Research ☐ Examination

10. Does your center have a skills-based simulation lab?

- ☐ Yes ☐ No

11. What is the skills-based simulation lab available for

- ☐ Skills practice, eg. HBB corner ☐ Teaching ☐ Research ☐ Examination

13. Which modality of simulation based training have you been exposed to?

- ☐ Manikin-based training (HBB)  
☐ Manikin-based training (NRT)  
☐ Manikin-based training (PALS)  
☐ Manikin-based training (ENCC)  
☐ Manikin-based training (BLS)  
☐ NRP eSIM™  
☐ HeartCode™ (PALS online course)  
☐ Online Basic Life Support course  
☐ Online ACLS course  
☐ Virtual Reality Simulation (VR)  
☐ Other (please specify below)

Other (please specify)

14. Are you aware of virtual reality simulation training?

- ☐ Yes ☐ No

15. When or where were you exposed to virtual reality simulation?

Confidential

Page 3 of 4

---

16. What are the challenges to online (computer-based or virtual reality) simulation?

- ☐ Lack of awareness about VR based simulation
- ☐ Lack of internet access
- ☐ Lack of standardized VR training modules
- ☐ Inconsistent power supply
- ☐ Lack of access to VR equipment and computers
- ☐ Other

---

Other (please specify)

\_\_\_\_\_

---

18. Are you aware that VR simulation can be run on a mobile phone so that you can learn skills on your own time and pace.

☐ Yes ☐ No

---

19. What type of mobile phone device do you own or use? (Choose all that apply)

- ☐ a. Tablet (e.g. Ipad, tablets)
- ☐ b. Smart Phone (e.g. Iphone, Samsung, Techno, Nexus, Infinix etc.)
- ☐ c. Feature phone (e.g. Does some gprs based activities)
- ☐ d. Basic (e.g. Used for call and SMS only)

---

20. What is the manufacturer and model of your phone/mobile device?

\_\_\_\_\_

---

21. If you are using an android enabled device, what android version does your device run (To find out, Goto [Settings->General->AboutDevice] and look for version number)

- ☐ a. Gingerbread (version 2.3)
- ☐ b. Ice Cream Sandwich (version 4.0)
- ☐ c. Jelly Bean (version 4.1 - 4.3)
- ☐ d. KitKat (Version 4.4)
- ☐ e. Lollipop (Version 5.0 - 5.1)
- ☐ f. Marshmallow (Version 6.0)
- ☐ g. Nougat (Version 7)
- ☐ h. Oreo (Version 8)
- ☐ i. Other

---

If Other, please specify

\_\_\_\_\_

---

22. Do you use mobile device (phone or tablet) currently for your work?

☐ Yes ☐ No

---

Please describe how you use your phone for work

*Confidential*

Page 4 of 4

---

25. If all facilities were available, would you recommend online simulation for training healthcare workers in your country?

☐ a. Yes ☐ b. No

---

If all facilities were available, would you recommend online simulation for your center?

☐ a. Yes ☐ b. No

---

26. Please state your reason(s)

Confidential

Follow Up Survey

Study ID

Please tell us a little about your participation in deliveries and ongoing HBB training in the last 6 months.

Approximately how many deliveries have you participated in during the last 6 months?

☐ none

☐ 1-5

☐ 6-10

☐ 11-15

☐ 16-20

☐ 21-25

☐ >25

How many deliveries have you participated in during the last 6 months that required resuscitation (at least one: bag-mask ventilation, chest compressions, intubation)?

Have you used the eHBB program in the last 6 months?

☐ No

☐ Yes

Have you watched the HBB neonatal resuscitation video in the last 6 months?

☐ No

☐ Yes

Please let us know about the quality of your training:

|                                                  | Strongly disagree     | Disagree              | Neutral               | Agree                 | Strongly agree        |
|--------------------------------------------------|-----------------------|-----------------------|-----------------------|-----------------------|-----------------------|
| eHBB was easy to access                          |  |  |  |  |  |
| eHBB was valuable for clinical practice          |  |  |  |  |  |
| eHBB was easy to navigate                        |  |  |  |  |  |
| eHBB had realistic graphics                      |  |  |  |  |  |
| eHBB provided valuable feedback                  |  |  |  |  |  |
| the HBB video was easy to access                 |  |  |  |  |  |
| the HBB video was valuable for clinical practice |  |  |  |  |  |
| the HBB video was realistic                      |  |  |  |  |  |

Did you have any technical difficulties with the refresher training (eHBB or HBB videos) between your in person simulations?

☐ Yes

☐ No

If yes, please explain:

Would you use this method of refresher training again?

☐ Yes

☐ No

*Confidential*

Page 2 of 2

---

If no, please explain:

---

---

If you weren't able to complete your assigned refresher training to watch the HBB video or do the eHBB at the 1, 3 or 6 month mark from your HBB course, please tell us which barrier(s) contributed?

- ☐ I didn't receive a reminder
  - ☐ The mHBS application didn't work
  - ☐ I had trouble accessing the refreshers on mHBS
  - ☐ I didn't have time to complete the refreshers
  - ☐ I didn't find the refreshers relevant
  - ☐ I didn't feel that I needed a refresher
  - ☐ I didn't remember about the refreshers
  - ☐ Other
- 

If you chose other, please tell us about the barriers you experienced with the refreshers

---

---

If you weren't able to complete your simulation practice at the 1, 3 or 6 month mark from your HBB course, please tell us which barrier(s) contributed?

- ☐ I didn't receive a reminder from the study personnel
  - ☐ The practice location was not convenient
  - ☐ I had trouble contacting the study personnel
  - ☐ I didn't have time to complete the practice
  - ☐ I didn't find the practice relevant
  - ☐ I didn't feel that I needed the practice
  - ☐ I didn't remember about the practice
  - ☐ Other
- 

If you chose other, please tell us about the barriers you experienced with attending the simulation practice

---

---

Other comments or concerns:

---

eHBB+mHBS/DHIS2 v.1

